## Assessment of safety

### Adverse events

#### Definitions

Adverse Event (AE)

According to GCP, an adverse event (AE) is defined as any untoward medical occurrence in a subject treated with a pharmaceutical product and which does not necessarily have a causal relationship with this treatment. An AE can therefore be any unfavourable and unintended sign (including an abnormal laboratory finding), symptom, or disease temporally associated with the use of a medicinal investigational product, whether or not related to that product.

An AE may be:

a new symptom or medical condition

a new diagnosis

a change in laboratory parameters

an intercurrent illness or accident

worsening of a medical condition/diseases existing before the start of the clinical trial

recurrence of a disease

an increase in frequency or intensity of episodic diseases.

Surgical procedures themselves are not AEs; they are therapeutic measures for conditions that require surgery. The condition for which the surgery is required may be an AE. Planned surgical measures permitted by the clinical trial protocol and the condition(s) leading to these measures are not AEs, if the condition leading to the measure was present before inclusion in the trial. In the latter case the condition should be reported as medical history.

Change in laboratory parameters: The criteria for determining whether an abnormal test finding should be reported as an adverse event are as follows:

- Test result is associated with accompanying symptoms, and/or
- Test result requires additional diagnostic testing or medical/surgical intervention, and/or
- Test result leads to a change in trial dosing outside of protocol-stipulated dose adjustments, or discontinuation from the trial, significant additional concomitant drug treatment, or other therapy, and/or
- Test result is considered to be an adverse event by the investigator or sponsor.

Merely repeating an abnormal test, in the absence of any of the above conditions, does not constitute an adverse event. Any abnormal test result that is determined to be an error does not require reporting as an adverse event.

Change in symptoms asked in the questionnaires:

Changes in a symptom asked in the symptom survey/questionnaire will be documented as an AE if the symptom worsened at least three grades (grade 1-10). Grade 0 corresponds to no complaints.

Serious adverse event (SAE)

A serious adverse event (SAE) is one that at any dose (including overdose):

- results in death
- is life-threatening1
- requires subject hospitalization or prolongation of existing hospitalization
- results in persistent or significant disability/incapacity² or
- is a congenital anomaly/birth defect
- is a important medical event³.

1 “Life-threatening” means that the subject was at immediate risk of death at the time of the serious adverse event; it does not refer to a serious adverse event that hypothetically might have caused death if it were more severe.

2 “Persistent or significant disability or incapacity” means that there is a substantial disruption of a person’s ability to carry out normal life functions.

3 Medical and scientific judgement should be exercised in deciding whether expedited reporting is appropriate in situations where none of the outcomes listed above occurred. Important medical events that may not be immediately life-threatening or result in death or hospitalization but may jeopardize the subject or may require intervention to prevent one of the other outcomes listed in the definition above should also usually be considered serious. Examples of such events include allergic bronchospasm requiring intensive treatment in an emergency room or at home, blood dyscrasias or convulsions that do not result in subject hospitalization, or the development of drug dependency or drug abuse. A diagnosis of cancer during the course of a treatment should be considered as medically important.

Clarification of the difference in meaning between "serious" and "severe":

The terms “serious” and “severe” are not synonymous but are often used interchangeably. The term ‘severe’ is often used to describe the intensity (severity) of a specific event (as in mild, moderate, or severe myocardial infarction); the event itself, however, may be of relatively minor significance (such as severe headache). This is not the same as “serious”, which is based on subject/event outcome or action criteria usually associated with events that pose a threat to a subject’s life or functioning. Seriousness (not severity) serves as a guide for defining regulatory reporting obligations.”

#### Assessment of AEs by investigator

Intensity/Severity

The intensity of an AE will be assessed by the investigator as follows:

| Mild: | Temporary event which is tolerated well by the subject and does not interfere with normal daily activities. |
| --- | --- |
| Moderate: | Event which results in discomfort for the subject and impairs his/her normal activity. |
| Severe: | Event which results in substantial impairment of normal activities of subject. |

Causal relation to trial medication/procedures

The investigator will evaluate the causal relationship of each AE with the administration of the investigational product(s) and/or trial procedures as follows:

| Related: | A reasonable possibility that the AE may have been caused by trial participation. A related event has a close temporal relationship to trial drug administration, and an alternative cause is unlikely. E.g. the AE abates upon discontinuation of trial participation and reappears when trial participation is continued. |
| --- | --- |
| Probably: | A reasonable possibility that the event is likely to have been caused by trial participation. The AE has a temporal relationship to the trial procedure(s) and follows a known pattern of response, but a potential alternative cause may be present. |
| Possibly: | A reasonable possibility that the event may have been caused by trial participation. The AE has a temporal relationship to the trial procedure(s); but does not follow a known pattern of response, and an alternative cause seems more likely, or there is significant uncertainty about the cause of the event. |
| Unlikely: | An AE that does not follow a reasonable temporal sequence from trial participation and that is likely to have been produced by the subject’s clinical state, other modes of therapy or other known aetiology. |
| Not related: | An AE that does not follow a reasonable temporal sequence from trial participation and that is definitely caused by the subject’s clinical state, other modes of therapy or other known aetiology. |
| Not assessable: | Inadequate data for assessment, no other data may be expected. |

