#### Immediate reporting by investigator

SAEs must be reported immediately within 24 hours after the SAE becomes known via facsimile using the "Serious Adverse Event" form to:

| IZKS Mainz  [name]  [contact] |
| --- |

The initial SAE Report must be as complete as possible including details of subject’s identification (screening number, random number), the (serious) adverse event (medical term, diagnosis), the trial medication and an assessment of the causal relationship between the event and the trial medication made by the investigator.

The investigator should provide related additional information on the clinical course and the outcome of each SAE as soon as possible via facsimile to IZKS Mainz using the SAE form (Follow up report).

The “Serious Adverse Event” forms are provided in the Investigator Site File.

The investigator must also inform the trial monitor in all cases. The sponsor will ensure that all legal reporting requirements are met.

In addition, any pregnancy diagnosed in a female subject or in the female partner of a male subject during treatment with the investigational product must be reported to the sponsor immediately via facsimile using the SAE form.

Worsening of a sign or symptom of the condition under treatment will normally be measured by efficacy parameters. However, if the outcome fulfils the definition of “serious adverse event”, it must be reported as such.

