## Analysis of adverse events

All summaries and listings of safety data will be performed for the safety population.

Frequencies of subjects experiencing at least one adverse event (AE) will be displayed by body system and preferred term according to MedDRA terminology. Detailed information collected for each AE will include: A description of the event, duration, whether the AE was serious, intensity, relationship to trial drug, action taken, clinical outcome. Summary tables will present the number of subjects observed with AEs and corresponding percentages. Additional subcategories will be based on event intensity and relationship to trial drug.

A subject listing of all AEs will be prepared.

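### AE causality is defined against study drug and/or trial procedures but tabulated as relationship to trial drug, so surgery-caused non-serious AEs can be counted as drug-related

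*Protocol*

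**What the plan says.** Protocol section 6.2.1.2 (Assessment of AEs by investigator) sets out the only causality scale in the document. The investigator is to rate the "causal relationship of each AE with the administration of the investigational product(s) and/or trial procedures as follows". The categories do not share one reference point:

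- *Related* opens with trial participation ("A reasonable possibility that the AE may have been caused by trial participation") and then adds a drug criterion: "A related event has a close temporal relationship to trial drug administration, and an alternative cause is unlikely".
- *Probably* is tied to procedures: "The AE has a temporal relationship to the trial procedure(s) and follows a known pattern of response". *Possibly* uses the same timing condition. Neither mentions the drug.
- *Unlikely* and *Not related* accept "other modes of therapy or other known aetiology" as the cause, but also require that the event lack a plausible time sequence from trial participation.

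Section 7.4 (Analysis of adverse events) lists what is collected for each AE, including "intensity, relationship to trial drug, action taken, clinical outcome", and says of the summary tables: "Additional subcategories will be based on event intensity and relationship to trial drug".

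For SAEs, section 6.2.1.5 (Immediate reporting by investigator) separately requires "an assessment of the causal relationship between the event and the trial medication made by the investigator".

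Section 5 (Trial schedule) makes Visit 2, Day -1, the last day of study drug and lists trabeculectomy on Day 0. Section 6.2.1.3 runs AE collection from consent to Visit 6, at week 24 and optional. Section 3.5.2 states that blinding does not apply.

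**The concern.** The item that section 7.4 tabulates is not the item that section 6.2.1.2 defines. The scale merges two possible causes, drug and procedure, and the table labels the result with one of them.

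This trial is poorly placed to absorb that mismatch. Study drug is given only before surgery, every patient in both arms is scheduled for trabeculectomy one day after the last dose, and most visits come after it. Early postoperative events are close in time to both causes.

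What is at stake is the descriptive comparison of tolerability. The Synopsis lists as a secondary objective that COSOPT-S should be descriptively superior to the reference therapy in tolerability and safety, and the drug-related AE table is a natural place to look for that. Counting surgical events there blurs the comparison. An analysis plan cannot repair this later, because a drug-specific rating that was never recorded cannot be recovered.

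**Working it through.** The protocol gives no figure for this point, so there is nothing to reproduce. The check is to follow one event through the text and then illustrate the effect with assumed rates.

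**Tracing an event.** Take a non-serious early postoperative complication of a recognised kind, such as a shallow anterior chamber in the first week.

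1. *Does it fit Related?* Not readily. That category requires close timing to drug administration with no likely alternative cause, and surgery is an obvious alternative.
2. *Does it fit Probably?* Yes, if trabeculectomy counts as a trial procedure. It has the required timing, follows a known pattern and may have another cause. If the pattern or cause is less clear, *Possibly* fits.
3. *Does it fit Unlikely or Not related?* Only if the event does not follow plausibly in time from trial participation. If surgery counts as part of participation, a first-week complication fails that condition, even though "other modes of therapy or other known aetiology" might otherwise describe its cause.
4. *Does trabeculectomy count?* The protocol does not say. For: it is an action in the trial schedule. Against: a planned trabeculectomy is an entry criterion (section 3.6.1), so it was decided independently of the trial. The text therefore supports opposite codings of the same event.
5. *Where does the rating go?* Under section 7.4, into subcategories by relationship to trial drug. A *Probably* or *Possibly* earned through surgery becomes a drug-related AE.

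**Illustration of size.** None of these rates is in the protocol; all are assumptions. Let p be the true proportion of patients with a drug-related AE, and s the proportion with an independent surgery-caused AE counted as drug-related. The observed proportion is

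p' = 1 − (1 − p)(1 − s),

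so with the same s in both arms the observed difference is (p1 − p2)(1 − s). With p1 = 50% and p2 = 20%:

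| s | Arm 1 | Arm 2 | Difference | Ratio |
|---|---|---|---|---|
| 0 | 50% | 20% | 30 points | 2.50 |
| 0.1 | 55% | 28% | 27 points | 1.96 |
| 0.3 | 65% | 44% | 21 points | 1.48 |
| 0.5 | 75% | 60% | 15 points | 1.25 |
| 0.7 | 85% | 76% | 9 points | 1.12 |

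For s = 0.3: 1 − 0.5 × 0.7 = 0.65 and 1 − 0.8 × 0.7 = 0.44, a difference of 0.21.

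Unequal attribution can move the contrast either way. With s = 0.3 applied in arm 1 only, the result is 65% against 20%, a difference of 45 points. Applied in arm 2 only, it is 50% against 44%, a difference of 6 points. These are extremes that show direction, not forecasts.

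**The case against.** The strongest reply is that this is a wording mismatch with limited reach. Much of that reply stands.

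- **SAEs.** A reader might infer that the mismatch also corrupts the decision on suspected unexpected serious reactions. The documents do not support that. Section 6.2.1.5 asks for causality to the trial medication, and section 6.2.1.6 leaves the workflow to a safety manual that is not shown. The point is confined to non-serious AEs.
- **The top category.** A reader might infer that a plainly surgical event would be rated *Related*. The drug-timing criterion there argues against it; only *Probably* and *Possibly* are open.
- **Other separators.** The causality split is not the only way to tell surgical from drug events. Section 7.4 also tabulates by body system and preferred term and lists every AE, AEs are asked about at Visit 2 before surgery, and several surgical complications are captured in the hypotension endpoint or the bleb classification. These help, but they do not correct the drug-related subcategories or settle ambiguous events.
- **The form.** The eCRF is not shown, and two entries are not excluded. Even so, the protocol describes one scale, and the one it describes is not drug-specific.
- **Certainty.** An investigator may treat the surgery as outside the trial and rate such events *Not related*. Misclassification is therefore possible rather than certain. That the same event can be coded either way is itself the defect.
- **Unmasked rating.** Differential attribution is a risk with any causality scale in an open-label trial, and two ratings would not remove it. They would make the question put to the rater explicit.

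**Conclusion.** The point holds in a limited form. The protocol defines AE causality against drug and/or procedures and reports it as relationship to drug, with trial procedures undefined. Followed as written, non-serious AEs caused by trabeculectomy can be rated *Probably* or *Possibly* and counted as drug-related.

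Equal misclassification in both arms multiplies the difference in drug-related AE proportions by (1 − s), assuming surgery-caused AEs are independent of drug-related ones and equally frequent in both arms. Unequal misclassification could shrink or inflate the difference. The protocol gives no complication rate, so no count of affected patients can be stated, and a reader should not infer one.

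The consequence is confined to a descriptive secondary comparison; the primary IOP analysis is untouched. The change is still worth making before data collection, because it is cheap then and cannot be made afterwards from the recorded ratings.

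**What to change.** In section 6.2.1.2 and on the AE page of the eCRF, replace the merged rating with two:

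- (a) relationship to the study drug, with every category worded in terms of drug administration rather than trial participation or procedures;
- (b) relationship to trabeculectomy or other trial procedures, with trial procedures defined so that it is clear whether the surgery and postoperative interventions are included.

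State in section 7.4 that all drug-related AE tables use (a) only, which brings them into line with the medication-specific assessment already required by section 6.2.1.5.

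The cost is one additional eCRF field per AE and wording changes in sections 6.2.1.2 and 7.4. Patients provide no further data, and neither the sample size nor the primary analysis changes.

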#### Period of observation and Follow-up

In this trial, the period of observation for collection of adverse events extends from the time the subject has signed the informed consent document up to Visit 6.

All subjects who have adverse events, whether considered associated with the use of the investigational products or not, must be monitored to determine the outcome. The clinical course of the adverse event will be followed up according to accepted standards of medical practice, even after the end of the period of observation, until a satisfactory explanation is found or the investigator considers it medically justifiable to terminate follow-up, but no longer than 30 days after the end of the trial.

Should the adverse event result in death, a full pathologist’s report should be supplied, if possible.

If the investigator detects a serious adverse event in a trial subject after the end of the period of observation, and considers the event possibly related to the prior trial, he should contact the sponsor to determine how the adverse event should be documented and reported.

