| IOP | Intraocular Pressure |
| ISF | Investigator site file |
| ITT | Intention to treat |
| KKS | Coordination Center for Clinical Trials (Koordinierungszentrum für Klinische Studien) |
| LKP | Clinical Trial Director according to AMG (Leiter der Klinischen Prüfung) |
| LSI | Last subject in |
| LSO | Last subject out |
| MedDRA | Medical dictionary for regulatory activities terminology |
| OCT | Optical Coherence Tomography |
| SAE | Serious adverse event |
| SAP | Statistical analysis plan |
| SDV | Source data verification |
| SUSAR | Suspected unexpected serious adverse reaction |
| TMF | Trial master file |

Synopsis

| Title | Investigation of the efficacy and safety of preoperative IOP reduction with preservative-free COSOPT-S® (dorzolamide/timolol, MSD) eye drops versus oral acetazolamide and dexamethasone eye drops and assessment of the clinical outcome of trabeculectomy in glaucoma patients |
| --- | --- |
| Short title | COSOPT-S®  Study |
| EudraCT | 2010-019975-30 |
| Sponsor trial code | 35131 |
| Indication | Glaucoma requiring trabeculectomy |
| Phase | IV |
| Treatments | Test product: COSOPT-S® (dorzolamide/timolol, MSD) eye drops b.i.d.  Reference therapy: oral acetazolamide 250 mg - 1500mg (DIAMOX®) per day (two or three doses), Preservative-free dexamethasone 1mg/ml eye drops five times per day |
| Primary objective | - To demonstrate that COSOPT-S® b.i.d is not inferior to the standard regimen in terms of IOP reduction three months after trabeculectomy. |
| Secondary objectives | - To show that the tolerability and safety of COSOPT-S® b.i.d. is descriptively superior to that of reference therapy - Comparison of the regimen COSOPT-S® b.i.d. with the reference regimen in terms of postoperative complications and the filtration bleb status three months after trabeculectomy - Exploration of patients’ satisfaction |
| Trial design | A prospective, active-controlled, open-label, randomized monocentric parallel group study |

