| Secondary endpoints | - Safety and tolerability of both treatment arms: Descriptive analysis of adverse events and questionnaires. - Number of necessary 5FU injections and suture lyses at Visit 5 - Required number of needlings and reoperations at Visit 5 - Change in IOP between Visit 1 and Visit 2 - Comparison between both groups of ocular hypotension rate (IOP 0-5 mm Hg, shallow anterior chamber, Descemet’s folds, choroid swelling, macular and choroidal folds) and filtration bleb classification in both groups at every postoperative visit. - Change in quality of life for the two regimens based on the NEI VFQ 25 quality-of-life questionnaire between Visit 1, Visit 2 and Visit 5 in both groups - Patients’ satisfaction (visual analogue scale) with pharmacologic intervention for IOP lowering - Change in status of conjunctiva |
| Statistical analysis | Change in IOP between baseline and three months post-OP was defined as the primary efficacy variable. A non-inferiority test on a one-sided level of significance α=0.025 will be carried out to show that treatment with Cosopt-S® b.i.d. (7:00 am, 7:00 pm; +/- 1 h) is not inferior to the reference preoperative treatment. Δ = 4 mm Hg was specified as the non-inferiority limit. The primary analysis will be conducted on the per protocol population. |

Trial schedule

| Visit  Action | Visit 1 Screening & Randomisation | Visit 2 | Surgery | Visit 3 | Visit 4 | Visit 5  (Primary  endpoint) | Visit 6 (optional  follow-up) |
| --- | --- | --- | --- | --- | --- | --- | --- |
| Trial day | -16 weeks to -28 days | Day -1 | Day 0 | Day 7±3 | Day 28±7 | Week 12±7days | Week 24±14 days |
| Demographics (sex, age) | **X** |  |  |  |  |  |  |
| Patient information and informed consent | **X** |  |  |  |  |  |  |
| Previous and concomitant diseases | **X** |  |  |  |  |  |  |
| Previous and concomitant treatments | **X** |  |  |  |  |  |  |
| Inclusion/exclusion criteria | **X** |  |  |  |  |  |  |
| Pregnancy Test (if applicable) | **X** |  |  |  |  |  |  |
| Laboratory tests (if applicable) | **X** |  |  |  |  |  |  |
| Trabeculectomy |  |  | **X** |  |  |  |  |
| Best-corrected visual acuity (ETDRS charts) | **X** | **X** |  | **X** | **X** | **X** | **X** |
| Non-contact Pachymetry |  | **X** |  | **X** |  | **X** |  |
| IOP | **X** | **X** |  | **X** | **X** | **X** | **X** |
| Optical Coherence Tomography |  | **X** |  | **X** | **X** | **X** | **X** |
| Axial length (IOL Master) |  | **X** |  |  | **X** |  |  |

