# TRIAL Treatments

## Investigational treatments

**Test product:**

28 days preoperatively (± 3 days): Discontinuation of all local antiglaucomatous drugs and IOP regulation with COSOPT-S® (dorzolamide 20mg/ml and timolol 5mg/ml, MSD) eye drops b.i.d. (7:00 am, 7:00 pm; +/- 1 h)

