**Reference therapy:**

Preoperative standard management of the Department of Ophthalmology, University Medical Center Mainz:

28 days preoperatively (± 3 days): Discontinuation of all local antiglaucomatous drugs and IOP regulation with oral acetazolamide 250 mg - 1500mg per day (two or three doses, dosis depending on IOP); potassium monitoring and potassium replacement if required.

7 days preoperatively (±1 day): Preservative-free dexamethasone 1mg/ml eye drops five times per day

All patients will be assigned to receive either test product or reference therapy formulations as per the randomization schedule. Both treatment phases have duration of four weeks. Treatment with study medication will be discontinued at the end of the study. The investigator will give the total quantity for the treatment phase of the investigational product to the eligible subject at visit 1. At the inclusion visit, each subject will be explained in detail the mode of administration of the test product and reference therapy, as well as a follow-up notebook in which the subject should report any deviations from the stipulated frequency of application, any problems of local tolerability, any adverse reactions, and any comments related to the study that he/she may wish to add.

If the subject is unable to read, the legally acceptable representative, according to the subject’s opinion, should fill in the follow-up notebook. At the last visit, all the investigational medicinal products (full, half-used or empty) must be returned to the investigator. If the products are not returned, the investigator will question the subject to determine the reason for this.

At each visit, any change in the frequency of administration of the test product will be recorded in the Case Report Form. This evaluation will be based, in particular, on the data recorded in the follow-up notebook given to each subject.

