# TRIAL schedule

Visit 1 (Screening visit): -16 to -4 weeks

The following data will be obtained/checked and documented:

- Patient information and informed consent
- Age
- Gender
- Medical history and concomitant medications
- In- and exclusion criteria
- Best corrected distance visual acuity (ETDRS charts)
- IOP (GAT) (schedule to return for all visits at the same time (± 1 hour) as Visit 1.
- Slitlamp examination (biomicroscopy)
- Grading of conjunctiva (ORA redness scale)
- Photography (conjunctiva)
- Non-contact pachymetry
- Symptom survey / Questionnaires
- Urine pregnancy test if the patient is a woman of childbearing potential
- Patient instruction: patients have to discontinue their current glaucoma medication(s), starting 28 days prior to surgery
- Randomisation
- Dispense of medication, explanation of application
- Dispense of follow-up booklet
- Schedule the patient to return for the next visit, according to date of planned surgery

Visit 2: Day -1

- Changes in medical health and/or concomitant medication
- Adverse events
- Last day of administration of study drugs
- Collection of study medication after last dose
- Checking compliance
- Symptom survey / Questionnaires
- Best corrected distance visual acuity (ETDRS charts)
- IOP (GAT) at the same time as Visit 1 (± 1h)
- Non-contact pachymetry
- Optical coherence tomography
- Axial length (IOL Master)
- Anterior chamber depth (AC or IOL Master)
- Slitlamp examination (biomicroscopy)
- Grading of conjunctiva (ORA redness scale)
- Photography (conjunctiva)
- Schedule the patient to return for the next visit

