**Visit 6 (Optional follow up): Week 24 ± 14 days**

- Changes in medical health and/or concomitant medication
- Adverse events
- Best corrected distance visual acuity (ETDRS charts)
- IOP (GAT) at the same time as Visit 1 (± 1h)
- Slitlamp examination (biomicroscopy)
- Filtration bleb classification (Grehn)
- Optical coherence tomography
- End of Trial

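### Section 7.4 does not split adverse events by onset, although four weeks of study drug sit inside a 16- to 42-week collection window that ends at an optional visit

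*Protocol*

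**What the plan says.** Section 6.2.1.3 sets the collection period for adverse events: it "extends from the time the subject has signed the informed consent document up to Visit 6". The schedule table dates Visit 1, with consent and randomisation, from minus "16 weeks to -28 days" relative to surgery. The last visit is headed "Visit 6 (Optional follow up): Week 24 ± 14 days".

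Study drug occupies a short part of this. Section 4.1 starts it at "28 days preoperatively (± 3 days): Discontinuation of all local antiglaucomatous drugs" and adds: "Both treatment phases have duration of four weeks". Section 5 lists under Visit 2, Day −1: "Last day of administration of study drugs".

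On analysis, Section 7.4 says: "Frequencies of subjects experiencing at least one adverse event (AE) will be displayed by body system and preferred term". It adds counts and percentages, subcategories by intensity and by relationship to trial drug, and a listing of all events by subject. Onset period is not among the stated breakdowns, and no narrower window is given for the tables. The synopsis states a secondary objective: "To show that the tolerability and safety of COSOPT-S® b.i.d. is descriptively superior to that of reference therapy".

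**The concern.** Avoiding the intolerance seen with four weeks of oral acetazolamide is a main part of the rationale in Section 1.1. The relevant comparison is therefore what happens to patients while they take the two regimens. A subject with at least one event under Section 7.4 could have had it on the previous drops before the first dose, on study drug, around the operation, or months later.

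Events outside the drug period that are equally common in both arms pull the two percentages together. Because the window ends at an optional visit, some patients are also observed longer than others, while the summary uses plain percentages. The tolerability estimate is then harder to read than it need be, in either direction.

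**Working it through.** The protocol gives no adverse-event rate or precision figure for these tables, so there is no planned figure to reproduce. What can be checked is the length of the windows and the direction of the effect.

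**1. Windows** (Sections 4.1, 5 and 6.2.1.3; drug course taken as 28 days, Day −28 to Day −1)

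- Consent to first dose: from 28 − 28 = 0 days to 112 − 28 = 84 days, that is 0 to 12 weeks (± 3 days).
- Shortest window with Visit 6: 28 + 154 = 182 days = 26 weeks. On-drug share 28/182 = 15.4%.
- Longest window with Visit 6: 112 + 182 = 294 days = 42 weeks. On-drug share 28/294 = 9.5%.
- Stopping at Visit 5 (nominal week 12): 28 + 84 = 112 days = 16 weeks, share 25.0%; up to 112 + 84 = 196 days = 28 weeks, share 14.3%.

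On-drug time is thus about 10 to 25% of the window.

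**2. Unequal follow-up.** Between patients who do and do not attend Visit 6 the difference is nominally 24 − 12 = 12 weeks.

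**3. Effect on the arm difference.** Let p_T and p_R be the risks of at least one event on drug (test and reference), and b a common risk off drug, independent of the on-drug risk. For each arm

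P(at least one) = 1 − (1 − p)(1 − b),

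so the tabulated difference is (p_R − p_T)(1 − b).

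Illustration with assumed rates p_T = 30% and p_R = 60% (not from the protocol; true difference 30 points):

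| b | Test | Reference | Difference |
| --- | --- | --- | --- |
| 20% | 44% | 68% | 24 points |
| 40% | 58% | 76% | 18 points |
| 60% | 72% | 84% | 12 points |
| 80% | 86% | 92% | 6 points |

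The direction is algebra; the size depends wholly on b.

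**4. Do the planned breakdowns already separate the periods?** Only in part.

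- *Preferred term.* The same formula holds row by row, with b the off-drug risk of that term. It matters little for terms that are rare off drug, which may apply to the paresthesia named in Section 1.1. It can matter more for redness, tearing or blurred vision, which Section 4.1.2 lists for dorzolamide and which can also follow eye surgery. Section 6.2.1.1 turns a worsening of at least three grades on the symptom survey into an adverse event, and the survey is repeated at Visit 5, so postoperative symptoms enter the same rows.
- *Relationship.* Section 7.4 speaks of relationship to trial drug, but Section 6.2.1.2 defines the grades largely against trial participation or trial procedures. The trial is open label, so the judgement is made with the arm known.

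**5. Can onset be assigned?** There is no visit at drug start, and adverse events are first scheduled at Visit 2, so pre-drug and on-drug events are assessed together. Section 7.4 names duration but not onset date.

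**The case against.** The strongest reply is that Section 6.2.1.3 defines collection, not analysis. Collecting from consent is no error, and Section 7.4 fixes no time window. A treatment-emergent definition is commonly left to the SAP, which Section 7 announces and which is not at hand. This stands as far as it goes: the missing definition alone would not be a finding. What remains is that the protocol does choose its breakdowns, chooses a weak one for attribution, and ends the window at a visit that not everyone need attend.

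Several stronger readings are tempting, and the documents do not support them.

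- *The on-drug signal is swamped.* This cannot be shown. The protocol gives no event rates for this window, and preferred-term rows and the relationship split separate some drug events.
- *Events outside the drug period cannot be due to the drugs.* This holds for events before the first dose. It does not hold for all postoperative events: Section 1.2 asks whether preoperative treatment affects the postoperative outcome, the synopsis makes postoperative complications a secondary objective, and Section 4.1.2 mentions choroidal detachment with aqueous suppressants after filtration procedures.
- *The superiority aim is a confirmatory claim without error control.* The objective is expressly descriptive, and Section 7.3.2 treats secondary analyses as exploratory.
- *Nothing else measures on-drug tolerability.* Questionnaires at Visit 1 and Visit 2 bracket the drug period and form part of this endpoint.

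Nor does anything suggest that attendance at Visit 6 will differ by arm. Unequal follow-up is therefore mainly a problem of interpretation, not demonstrated bias.

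**Conclusion.** The point holds as a cheap and worthwhile improvement to a descriptive secondary analysis. Four weeks of treatment are about 10 to 25% of the collection window, and onset period is not among the stated breakdowns. Any off-drug risk common to both arms shrinks the difference in subjects with at least one event by 1 − b. This assumes equal off-drug risk in the arms and independence from the on-drug risk; its size is unknown. Follow-up can differ by up to about 12 weeks between patients. The planned relationship split is a weak safeguard. The primary non-inferiority test and the sample size are not affected.

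**What to change.** In Section 7.4, add adverse-event tables by onset period:

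- First dose to surgery: the tolerability comparison, given as the risk difference in subjects with at least one event with a 95% CI, labelled exploratory.
- Surgery to Visit 5: reported separately as postoperative safety.
- Before first dose and after Visit 5: listings only, which removes the unequal tail from the comparison.

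In the synopsis, replace the aim of showing descriptive superiority by a descriptive comparison of tolerability using that estimate and interval. Confirm that the eCRF records the onset date of each event and the date of first dose. Reconcile the final-visit label, which Section 5 attaches to Visit 5 and the schedule table to Visit 6.

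The cost is some rewording and a few extra tables, plus a date field if onset or first dose is not yet captured. Visits and treatment do not change.
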